### Interim analyses {21b}

The three main researchers will have access of the interim analyses, and they will have access to these interim results and make the final decision of the trial.

### Methods for additional analyses (e.g., subgroup analyses) {20b}

Two-way mixed effect ANOVA will be used to compare intergroup e intragroup (pre- and post-intervention) changes for additional analyses, considering significant a *p* value < 0.05.

### Methods in analysis to handle protocol non-adherence and any statistical methods to handle missing data {20c}

For the missing data, multiple data imputation will be used, performing 20 different random imputations and verifying the constancy of the differences found between the groups, a result will be considered consistent if most of the imputations led to a result according to the study hypothesis.

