### Strategies to improve adherence to interventions {11c}

The patients will be instructed to record exercise habits on a diary during the week, and they will be asked to return the information at the end of the 8-week period; furthermore, the educational session will address the issue of adherence. Outcome data is to be collected for participants who discontinue from intervention protocols and the reason why the patient discontinued and how long the patient completed the protocol. The presence of 75% in the session will be considered a positive adherence.

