### Participant timeline {13}

#### Sample size {14}

The sample size is calculated using the results of a ten-patient pilot study, and considering an effect size of 0.33, an expected power of 80% and alpha-error 5%, 36 patients will be needed and dropout is considered 20%, a total of 50 patients. For the missing data, multiple imputations followed by a sensitivity analysis will be conducted. The pilot study is unpublished in other ways of publication.

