#### Assignment of interventions: allocation

### Sequence generation {16a}

The allocation sequence is generated by an advisor who is neither the intervention physiotherapist nor the evaluator, using an online program (Random.org) that generates the sequence of numbers for randomization patients that will be randomized in two groups: instruction group (IG) and supervised group (SG).

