## Statistical methods

### Statistical methods for primary and secondary outcomes {20a}

Data entry will be managed by a blinded assessor (not involved in rehabilitation), and the data will be recorded in a documents clouds. All data will be analyzed by Statistical Package for the Social Sciences (SPSS) version 21.0. Two-way mixed effect ANOVA will be used to compare intergroup e intragroup (pre- and post-intervention) changes, considering significant a *p* value < 0.05.

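### Agreement among 20 random imputations shows imputation noise, not whether the missing-data assumption holds, and no other check is defined

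*Protocol article*

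**What the plan says.** Two places in the protocol article deal with missing outcomes.

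- *Sample size {14}*: "For the missing data, multiple imputations followed by a sensitivity analysis will be conducted". The content of that sensitivity analysis is not given.
- *Methods in analysis to handle protocol non-adherence and any statistical methods to handle missing data {20c}*: multiple imputation, "performing 20 different random imputations and verifying the constancy of the differences found between the groups". The decision rule follows: "a result will be considered consistent if most of the imputations led to a result according to the study hypothesis".

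Section {20c} names no imputation model and no alternative assumption about the unseen values. It contains the only check that the article describes.

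A third passage, *Strategies to improve adherence to interventions {11c}*, bears on how much will be missing: "Outcome data is to be collected for participants who discontinue from intervention protocols and the reason why the patient discontinued".

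**The concern.** Repeated random draws under one assumption vary only through chance in the filling-in. Their spread measures imputation noise. If patients who do not return for the post-programme 6MST are worse than returning patients with the same baseline, every draw carries the same error and the draws still agree. The label attached by {20c} would then be earned whether or not the assumption behind it is true.

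This is separate from how the 20 results are combined. Pooling by Rubin's rules would put right the standard error, but the check would remain blind to informative loss.

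Arm-related loss is plausible in this design. The supervised group (SG) travels to the laboratory every week for 8 weeks, while the instruction group (IG) has one supervised session and then trains at home. *Background, rationale {6a}* names travel difficulty from poor physical condition and limited mobility as a barrier to rehabilitation. That burden falls mainly on SG and is tied to the capacity that the 6MST measures. At stake is a between-group difference, produced partly by who came back, that is reported as consistent.

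**Working it through.** **Inputs from the protocol**

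- 20 draws and a majority rule ({20c}).
- Missing share: "36 patients will be needed and dropout is considered 20%, a total of 50 patients" ({14}). The total of 50 does not follow from these figures: 36/(1 − 0.20) = 45, while 1 − 36/50 = 0.28. That figure is not the subject here. It is the reason for working with both 20% and 28%.
- Patients are "randomized in two groups: instruction group (IG) and supervised group (SG" ({16a}).
- Analysis: "Two-way mixed effect ANOVA will be used to compare intergroup e intragroup (pre- and post-intervention) changes" ({20a}). With two time points, the group-by-time test equals a t-test on change.

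**Assumptions, not in the protocol**

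25 patients per arm, outcome SD 1, no true effect, pre–post correlation 0.6 or 0.7, missing-at-random imputation from one model, and 3,000 simulated trials per setting.

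**Step 1: bias by arithmetic**

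Missing-at-random imputation fills each gap as if the patient resembled observed patients with the same baseline and arm. If the true values are lower by δ SD in an arm with missing share p, that arm's mean is overstated by p × δ. Hence

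bias in (SG − IG) = p_SG × δ_SG − p_IG × δ_IG.

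- 20% missing per arm, only SG affected: 0.20 × 0.5 = 0.10 SD; 0.20 × 1 = 0.20 SD.
- 28% missing per arm, only SG affected: 0.28 × 0.5 = 0.14 SD; 0.28 × 1 = 0.28 SD.
- 30% missing in SG, 10% in IG, 1 SD in both: 0.30 − 0.10 = 0.20 SD.
- Only IG affected, 20% missing: −0.10 or −0.20 SD, that is, against SG.
- Same share and same shift in both arms: 0.
- If follow-up of discontinuers cuts missingness to, say, 10%: 0.10 × 0.5 = 0.05 SD; 0.10 × 1 = 0.10 SD.

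**Step 2: false positives with Rubin pooling (correlation 0.6)**

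| Setting, no true effect | Bias (SD) | Rejections | Draws agreeing, among significant trials |
|---|---|---|---|
| 20%/20%, no shift | – | 4.4% | 90% |
| 20%/20%, SG shift 0.5 SD | 0.097 | 6.0% | 90% |
| 20%/20%, SG shift 1 SD | 0.194 | 10.6% | 91% |
| 30% SG/10% IG, 0.5 SD in both | 0.100 | 6.0% | – |
| 30% SG/10% IG, 1 SD in both | 0.197 | 10.2% | 90% |

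The simulated biases match Step 1.

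**Step 3: the majority rule of {20c} itself (correlation 0.7, 20% missing per arm)**

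Here a draw counts as agreeing with the hypothesis if it is significant in favour of SG. Dropout depends on the unseen outcome; the slope is the log-odds per residual SD.

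| Dropout | Bias (SD) | SD between draws | Mean agreement of the 20 verdicts | Majority declares SG benefit |
|---|---|---|---|---|
| Random | 0.01 | 0.10 | 97% | 3.8% |
| SG only, slope 1 | 0.14 | 0.10 | 94% | 12% |
| SG only, slope 2 | 0.20 | 0.10 | 92% | 18% |
| Both arms, same direction, slope 1 | 0.00 | 0.10 | 97% | 5% |

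At 28% missing, the two SG-only rows give bias 0.19 and 0.27 SD and false declarations of 18% and 29%.

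The spread between draws stays flat while bias and false declarations rise. Agreement slips by a few points but stays far above a majority. The slip is no warning signal either: a genuine effect of the same size would also move trials nearer the significance boundary.

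The percentages in Steps 2 and 3 are not interchangeable. Step 2 counts rejections by a pooled test, and Step 3 counts majority verdicts in favour of SG.

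**The case against.** The strongest case against this point has four parts.

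1. *Sections {14} and {20c} may describe two different steps.* Section {14} places a sensitivity analysis after imputation, and {20c} never calls its constancy check by that name. A full protocol or analysis plan could define a proper one. This stands as far as it goes: an undefined sensitivity analysis in an article is no fault in itself. But {20c} does fix a check and a verdict rule, and that stated rule is uninformative about the assumption.
2. *The model is inferred.* No imputation model is stated, so a single missing-at-random model is a reading of the text. It is the natural one, because no second model or assumption appears.
3. *Missingness may be well below 20%.* Section {11c} plans outcome collection after discontinuation, and bias falls in proportion to what remains missing. This stands. It reduces the problem but does not test the assumption about values that stay missing.
4. *The harm needs particular conditions.* Loss must differ by arm, in amount or in kind. The protocol gives no data on this. Its remark that soreness and fatigue lead patients to abandon treatment concerns non-individualized programmes. At 0.5 SD the excess is small (6.0% against 4.4%), and the figure near 10% needs a full 1 SD shift. Loss in IG would bias against SG. All of this stands and limits the size of the point.

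A reader might also infer that the protocol claims its result will be robust to missing data. It does not: its word is consistent, defined as a majority of draws agreeing with the hypothesis.

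**Conclusion.** The point holds in a limited form. The check fixed in {20c} cannot tell a sound result from one distorted by arm-related informative loss, because agreement among redraws reflects imputation noise. No other check is described.

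Under an assumed 20% missing, a shift in one arm biases the difference by about 0.10 SD (0.5 SD shift, false positives about 6%) to about 0.20 SD (1 SD shift, about 10%), in either direction. Under the majority rule, outcome-dependent loss in SG raised false declarations of SG benefit from 3.8% to 12–18%. These sizes rest on the assumed arm sizes, correlation, imputation model and dropout pattern. The blindness of the check requires only that the draws share one assumption.

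The documents do not show that dropout will be informative or that the trial's result will be biased. The rule should be changed before results by arm are seen, but it does not undermine the design.

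**What to change.** In {20c}, replace the constancy and majority check with one multiple-imputation analysis of the 6MST, pooled by Rubin's rules, as the reference. Then define the sensitivity analysis promised in {14} as a delta-adjusted (tipping-point) analysis:

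- worsen imputed post-programme 6MST values by a prespecified range, for example 0.25, 0.5, 0.75 and 1.0 SD, separately in SG and IG;
- re-pool each time and report the smallest shifts, by arm, that change the conclusion;
- read those shifts against the discontinuation reasons collected under {11c}, and describe the result as consistent only if they are clinically implausible.

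Unlike redrawing, this check responds to the assumption: worsening imputed SG values by D SD lowers the difference by 0.20 × D at 20% missing. The estimate reaches zero at D = estimated difference/missing share, and significance is lost sooner.

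The cost is a few lines of code and a short change of text, with no new data. The downside is that the consistency statement may turn out less favourable.

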### Trial design {8}

This is a descriptive protocol of a clinical trial, randomized, single-blinded, and type of framework is superiority.

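### The 20 imputed analyses are turned into a conclusion by majority vote, which leaves out between-imputation variance and raises the type I error above 5%

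*Protocol article*

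**What the plan says.** The protocol article deals with missing data in two places.

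- Section {20c} makes multiple imputation the method for missing data, "performing 20 different random imputations and verifying the constancy of the differences found between the groups". It then sets the criterion: "a result will be considered consistent if most of the imputations led to a result according to the study hypothesis".
- Section {14} says "For the missing data, multiple imputations followed by a sensitivity analysis will be conducted", and describes neither step further.

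Three other statements bear on the point. Section {8} declares a superiority framework. Section {20a} tests with a two-way mixed ANOVA at p < 0.05. Section {14} expects 20% dropout and a total of 50 patients. No section names pooling of estimates or variances, or any other way to combine the 20 results.

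**The concern.** Multiple imputation gives valid inference because its total variance has two parts: the average variance within a completed data set, and the variance between data sets, which reflects how uncertain the imputed values are. A test in one completed data set uses the first part only. Counting how many such tests agree gives 20 correlated answers, each with a standard error that is too small, and the second part is never restored.

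Three consequences follow.

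1. A vote on significance rejects too often when there is no effect.
2. There is no single difference, interval or p-value to report, which a superiority trial tested at 5% needs.
3. The criterion recognises only results that agree with the hypothesis. It has no counterpart for a null or opposite result, so it leans towards a positive answer.

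This is not detail left to a fuller document. The article states a rule, and the rule is wrong.

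**Working it through.** **Inputs from the article.** 20 imputations and a majority criterion ({20c}); p < 0.05 ({20a}); two groups ({16a}); 50 patients, 36 needed, 20% dropout ({14}). Going from 50 to 36 is a loss of 1 − 36/50 = 28%, so 28% is shown beside 20%.

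**Assumptions.** 1:1 allocation (25 per arm); post values missing completely at random and about equally in both arms; pre/post correlation 0.5 or 0.8; imputation by Bayesian normal regression on baseline and group; *most* read as at least 11 of 20.

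**Analytic approximation.** Let W be the average within-imputation variance and λ the fraction of missing information. The pooled estimate has variance of about W/(1 − λ). The vote is positive roughly when the estimate exceeds 1.96·√W in absolute value, so under the null

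α ≈ 2·[1 − Φ(1.96·√(1 − λ))].

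- λ = 0.10: 1.96 × √0.90 = 1.859, α ≈ 6.3%
- λ = 0.20: 1.96 × √0.80 = 1.753, α ≈ 8.0%
- λ = 0.28: 1.96 × √0.72 = 1.663, α ≈ 9.6%
- λ = 0.40: 1.96 × √0.60 = 1.518, α ≈ 12.9%

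**Simulation under no true difference.** 10,000 trials per row. With two groups and two time points, the group-by-time test of the planned ANOVA equals a t test on change, so that test was applied to each completed data set. Rubin's rules used Barnard-Rubin degrees of freedom. The plan's own figure here is the nominal 5%; the complete-case test reproduces it, so the simulation is calibrated.

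| Post values missing | Correlation | Mean λ | Complete case | Rubin's rules | Vote, significant in either direction | Vote, significant in the hypothesised direction (nominal 2.5%) | Vote, direction only |
|---|---|---|---|---|---|---|---|
| 8% (2 of 25 per arm) | 0.5 | 0.07 | 4.9% | 4.8% | 5.6% | 2.7% | 50% |
| 20% | 0.5 | 0.17 | 5.0% | 4.8% | 7.1% | 3.5% | 49% |
| 20% | 0.8 | 0.20 | 5.0% | 4.6% | 7.6% | 3.8% | 49% |
| 28% | 0.5 | 0.24 | 5.0% | 4.7% | 8.2% | 4.3% | 49% |
| 40% | 0.5 | 0.35 | 5.0% | 4.4% | 10.9% | 5.3% | 48% |

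The Monte Carlo standard error near 7% is √(0.07 × 0.93/10,000) = 0.26 percentage points.

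**Stability.** A repeat with another seed gave 5.6 to 6.3% with 5 of 50 missing, 7.5 to 8.1% at 20% and 8.4 to 9.0% at 28%. Runs of 4,000 trials with correlation 0.5 to 0.7, using both change-score and baseline-adjusted (ANCOVA) tests, gave 7.3 to 8.7% at 20% and 8.6 to 9.5% at 28%. Rubin's rules stayed at 4.2 to 5.3% in both sets of runs.

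**What pooling would overturn.** At 20% missing, the vote was positive in the hypothesised direction while the pooled p-value was 0.05 or more in 1.13% of trials (correlation 0.5) and 1.55% (correlation 0.8). As shares of the vote's false positives in that direction, these are 1.13/3.49 = 32% and 1.55/3.78 = 41%.

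**The case against.** The strongest defence is that {20c} speaks of constancy and of a result being consistent, not of significance. On that reading the significance test is the mixed ANOVA in {20a}, the vote is a robustness check beside it, and the rates above are not the trial's type I error. The wording allows this reading. But {20c} makes imputation the handling of missing data, {14} places the sensitivity analysis after imputation, and no other analysis of the imputed data is stated. Even as a check, the vote would certify results whose properly pooled p-value exceeds 0.05.

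Three further objections limit the size but not the defect.

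- **The rule is undefined.** The article gives no number for *most*, and does not say whether an imputation must be significant or only point the right way. The error rate depends on this: about 7 to 9% for significance in either direction at 20% missing, 3.5 to 3.8% in the main runs for significance in the hypothesised direction, about 49% for direction alone. The middle figure lies below 5%, but its proper benchmark is 2.5%. No reading holds its nominal level.
- **Dropout is not the same as a missing outcome.** Section {11c} plans to collect outcomes from participants who discontinue the intervention, so fewer than 20% of post values may be missing. At about 10% missing the inflation is small, about 6%.
- **Correlation and allocation ratio are not in the article.** They are assumptions. The lack of a pooled estimate and interval, and the one-way criterion, do not depend on them.

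**Conclusion.** The rule is wrong as written and must be changed before the analysis. A vote over 20 imputed data sets is not a valid way to combine them: it drops the between-imputation variance, produces no reportable effect with an interval, and favours the hypothesis. Read as significance in at least 11 of 20, it turns a 5% test into one of about 7 to 9% at 20% missing and about 8 to 10% at 28%, where Rubin's rules hold about 4 to 5%. The excess is moderate at the planned dropout, small if few outcomes are missing, and larger as missingness grows. These sizes rest on the assumptions listed with the calculation. That the vote settles the primary comparison is an inference from its being the only combining rule stated, but it fails as a robustness criterion too.

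**What to change.** Replace the majority criterion in {20c} with Rubin's rules. In each of the 20 data sets, estimate the supervised-minus-instruction difference in change in 6-min step test count. Pool the estimate and its variance, and report one difference, one 95% CI and one p-value with small-sample (Barnard-Rubin) degrees of freedom. Because the group-by-time test reduces to a difference in change scores, only one scalar has to be pooled. Do the same for the secondary outcomes.

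Describe the sensitivity analysis announced in {14} separately. Judge robustness by comparing the pooled estimate and interval with the complete-case ones, not by how many imputations fall below 0.05.

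The cost is one sentence in the analysis section. The imputations are already planned and no further data or patients are needed. The pooled p-value will usually be slightly less favourable than the vote suggests, because it carries the uncertainty that the vote leaves out.

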### Plans to give access to the full protocol, participant level-data, and statistical code {31c}

The datasets analyzed during the current study are available from the corresponding author on reasonable request.

## Oversight and monitoring

### Composition of the coordinating center and trial steering committee {5d}

The coordinating center is situated at the Spirometry and Respiratory Physical Therapy Laboratory of the Federal University of São Carlos (UFSCar) and comprises laboratory researchers. They are responsible for all local organization aspects such as identifying potential recruits, orientation support, and minimal equipment and room structure.

The Trial Steering Committee (TSC) consists of two laboratory researchers who are responsible for supervising the trial, as for instance concealment of blind allocation and evaluation of how the trial is conducted. They will meet once a month. There is no public Involvement Group (SPIG).

### Composition of the data monitoring committee, its role and reporting structure {21a}

Data monitoring committee is not considered as this is a low-risk intervention.

### Adverse event reporting and harms {22}

Adverse events (AEs) are not anticipated. The potential minor AEs that may be anticipated are fatigue, tachycardia, or blurred vision during the exercise that will be minimized by monitorization before and after the assessment and intervention. If the symptoms are persistent, the physiotherapist will immediately stop the exercise and conduce the first aid.

All protocol violations and all adverse-events could be registered and reported in the final paper and the adverse event could be report by the Ethics Committee of the Federal University of São Carlos.

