### Action for randomized groups

#### Instruction group (IG)

Patients will have one physiotherapist-supervised session, which will be the first day of PRP. In that session, this group will receive a personalized booklet that will be read together with the physiotherapist and all exercises will be explained and performed together with the physiotherapist and they will be oriented self monitoring of vital signs and symptoms. On the next 7 weeks of PRP, the patient will execute the exercises at home with equipment they have at home (chair, step, food packages) and if they have any questions/doubt, they to call the physiotherapist. In addition, patients will record exercise habits on a diary during the week and they will be asked to return the information at the end of the 8-week period.

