#### Supervised group (SG)

Patients will receive the same booklet as the IG (education session) and, for an 8-week period, they will have a weekly supervised physiotherapy session (at laboratory) where they will perform the same training they perform at home. All patients will be encouraged to exercise at home following the booklet four times every week and they will be oriented self monitoring of vital signs and symptoms .

During the supervised sessions, patients will be monitored regarding pulse oximetry and Borg scale, recording the values on a vital sign monitoring form (Additional file 4) and the clinical evolution form will be filled out by a physiotherapist.

At the end of PRP, patients of both groups will undergo reassessment (the same executed pre-rehabilitation, except for spirometry).

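### Adverse event recording is optional as worded, and the described contacts give the supervised group more chance of detection, so counts by arm are probably not comparable

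*Protocol article*

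**What the plan says.** **Recording rule.** Under Adverse event reporting and harms {22}: "all adverse-events could be registered and reported in the final paper". Reporting to the ethics committee is put in the same conditional form. The section opens with "Adverse events (AEs) are not anticipated", then names fatigue, tachycardia and blurred vision as possible minor events. If symptoms persist, "the physiotherapist will immediately stop the exercise and conduce the first aid".

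**SG.** Under Supervised group (SG), patients attend the laboratory weekly for 8 weeks. "During the supervised sessions, patients will be monitored regarding pulse oximetry and Borg scale, recording the values on a vital sign monitoring form", and a physiotherapist completes a clinical evolution form. They also train at home.

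**IG.** Under Instruction group (IG), there is one supervised session on the first day. For the following 7 weeks patients train at home, and "if they have any questions/doubt, they to call the physiotherapist".

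**Other information flows.** The diary covers exercise habits (Instruction group; Strategies to improve adherence {11c}). Under Other important information about the study, IG patients are asked at reassessment about adherence, and SG patients are asked weekly about exercise frequency. Reasons for discontinuing are collected {11c}. Patients with discomfort are directed to a health professional, with no stated report back to the trial {11b}. Both groups are reassessed after the programme.

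**Oversight.** "Data monitoring committee is not considered as this is a low-risk intervention" {21a}. A two-person steering committee reviews conduct monthly.

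**The concern.** Supervision is the randomised factor, and it also governs how often trial staff see a patient. An event in SG can be witnessed at a session or mentioned a week later. An event in IG may have to be volunteered by phone, or remembered until reassessment. If the paper tabulates adverse events by arm, part of any difference will come from who was seen rather than from who was harmed.

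The probable direction makes the unsupervised programme look safer. That matters because the Introduction names muscle soreness, fatigue and abandonment of treatment as consequences of over-prescription. Participants have an mMRC grade of at least 2, and the Discussion foresees use at home and in other patient groups. A remark that the home programme produced few events could simply mean that nobody had asked. The conditional wording adds a second problem, since as written it does not commit the trial to recording events in either arm.

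**Working it through.** The article states no adverse event rate, count or power, so there is no figure to reproduce. The check compares the described contacts and then illustrates what unequal detection could do.

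**1. Contacts, by arm**

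| Route | SG | IG | Said to ask about harms? |
|---|---|---|---|
| Supervised sessions | 8 | 1 | No; oximetry, Borg and a clinical evolution form are described for SG |
| Call made by the patient | not described | yes, for questions or doubts | No |
| Diary returned at 8 weeks | yes, reading {11c} as both arms | yes | No; exercise habits |
| Staff question | weekly, exercise frequency | at reassessment, adherence | No |
| Reason for discontinuing | yes | yes | Only incidentally |
| Post-programme reassessment | yes | yes | Not stated |

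No row is a harms question common to both arms. The rows that differ favour detection in SG.

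**2. Share of sessions observed**

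Assumption: four home sessions a week in both arms. The frequency appears in the SG section only.

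- SG: 8 / (8 + 8 × 4) = 8/40 = 20%.
- IG, home training in 7 weeks: 1 / (1 + 28) = 1/29 = 3.4%.
- IG, home training in 8 weeks: 1 / (1 + 32) = 1/33 = 3.0%.
- Ratio: 20/3.4 to 20/3.0, or 5.8 to 6.6 with unrounded shares.

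This is a ratio of observed sessions, not of events captured: 32 of 40 SG sessions are also unobserved.

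**3. Illustration of the effect on counts**

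Assumptions, none from the documents: 50 patients split 25 and 25; the same true 8-week risk of 20% in both arms; detection of 90% in SG.

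Expected recorded cases = patients × true risk × detection.

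| Detection in IG | SG cases | IG cases | SG/IG |
|---|---|---|---|
| 90% | 25 × 0.20 × 0.9 = 4.5 | 4.5 | 1.0 |
| 70% | 4.5 | 3.5 | 1.3 |
| 50% | 4.5 | 2.5 | 1.8 |
| 30% | 4.5 | 1.5 | 3.0 |

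At 30% detection, the chance that IG records no event at all is (1 − 0.20 × 0.3)^25 = 0.94^25 = 0.21. The ratio depends only on the two detection rates; a different true risk changes the counts but not the ratio.

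**4. Exposure also differs**

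On the session counts in step 2, SG trains 40/33 to 40/29 = 1.21 to 1.38 times as often as IG. If risk rose with sessions, SG would truly have more events by roughly the amount at the low end of step 3. A raw difference in counts could not separate the two.

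**5. What a zero would mean**

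Even with complete capture, 0 of 25 is compatible with a true risk of up to 1 − 0.05^(1/25) = 11.3% (one-sided 95% bound).

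**The case against.** The best reply is that this is an article. The monitoring form, the booklet and the vital sign form are additional files not shown here, and the data collection forms are held by the corresponding author. Any of them may contain a symptom item. Both arms are taught to monitor their own symptoms, all patients have medical support, and the conditional wording may be a language slip for *will be*. Completion was expected in June to August 2021, so a new checklist would reach few patients.

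Part of this stands: the absence of a harms item from the unseen forms cannot be asserted. The reply does not remove the unequal contact schedule, which is stated, or the non-committal rule, which is also stated.

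A reader might infer four stronger things, which the documents do not support:

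- *That events are actively sought each week in SG.* The article describes physiological monitoring, a clinical evolution form and a question on exercise frequency, but no harms question.
- *That a phone call is the only route in IG.* The call is for questions, and the diary, the reassessment or a discontinuation reason could each reveal an event.
- *That the counts are certain to be biased.* This depends on unknown detection rates and on the unseen forms.
- *That comparative safety is part of the trial's stated question.* The objective compares results with and without weekly supervision, the listed outcomes include no safety outcome, and the harms section promises no comparison by arm.

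Nor is the trial without oversight: the steering committee meets monthly, although no review of events by arm is described.

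**Conclusion.** The point holds in a limited form. As written, recording of adverse events is optional, and the described contacts tie the chance of detecting one to allocation: eight monitored sessions in SG against one in IG. Any counts reported by arm are likely to be affected, most probably by under-counting in IG, and home events may be missed in both arms. The direction follows from the schedule. The size is unknown: the SG/IG ratios of 1.3 to 3.0 rest wholly on assumed detection rates, equal true risk and an even split of 50 patients. The primary outcome analysis is not affected. What is at risk is any safety statement that sets one arm against the other, or that calls the home programme free of events.

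**What to change.** 1. In Adverse event reporting and harms {22}, change *could be* to *will be*, both for registration and reporting in the paper and for reporting to the ethics committee.
2. Collect adverse events in both arms with the same short checklist at the same times: one item added to the 8-week diary, and a standard set of questions at the post-programme reassessment.
3. Have the questions asked by someone other than the blinded evaluator, since the answers can reveal the arm. The main researcher is a candidate, being described as outside randomisation, evaluation and intervention {26a}.
4. List events seen only in SG laboratory sessions separately, and make no between-arm harms statement except from the common source.

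The cost is small: a diary item, a one-page checklist at a visit that already takes place, and a few sentences of text, with no new visit or staff. The downsides are a little more data entry and incomplete coverage. Patients who have already finished have only spontaneous reports, and the paper must say so. Given the expected completion dates, that may be most of them. Steps 1 and 4 can still be applied to the reporting of the whole trial.
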